### Treatment of Subjects

#### Conservative treatment

Patients randomised for conservative treatment are treated according to the current daily practice. In other words, conservative treatment is determined by the preferences of the treating physician. Conservative treatment may consist of expectant management, antibiotics and/or analgetics. Should there be radiologic evidence for the presence of pericolic abscesses, percutaneous drainage may be performed depending on the size and opinion of the local radiologist regarding accessibility.

#### Elective surgery

Patients randomised for elective surgery will undergo an elective colonic resection within approximately 6 weeks. In the interval between randomisation and elective surgery, patients are treated conservatively (see above). Intentionally, a laparoscopic approach is used. The extent to which the colon is resected in the proximal direction should cover the entire macroscopically involved colon. In other words, the proximal resection line should be where no diverticula exist or at the level where a considerable decline in number of diverticula is noted. Distally, the margin of resection should be where the taenia coli splay out onto the upper rectum. After resection a primary anastomosis will be performed between the distal colon and rectum.

#### Randomisation (figure 1)

**Figure 1 F1:**
[figure not shown]
Flowchart DIRECT trial

All patients presenting themselves with persisting abdominal complaints after an episode of diverticulitis and/or a third (or more) diverticulitis recurrence, require to have had a recent radiological examination of the abdomen. Preferably a CT-scan is used. However, ultrasonography may also be used on the condition that bowel wall thickening and abscess size can be assessed accurately. Colonoscopy may be performed on indication to exclude malignancy.

If all inclusion criteria are met, patients are informed about the study protocol by their treating physician. They are given a 3 day reflective period, together with the information package. After the reflective period, the patient is contacted and asked for participation. If the patient decides to take part in the trial, he/she is invited to the local hospital to sign the informed consent. After receiving this consent form, randomisation will be performed centrally by the study coordinator using block randomisation (block size 6) stratified for center and inclusion criteria (persisting abdominal symptoms or frequent recurrences).

Both patients in the conservative and elective resection group will be treated conservatively in case of events during follow-up unless there is an absolute indication for surgery according to the treating physician (e.g. fistula, symptomatic stenosis, perforation with purulent/fecal peritonitis). In addition, in case of persisting abdominal symptoms during follow-up (in the conservative group) which are regarded as unbearable by both patient and treating physician, the treating physician may consult an independent event adjudication committee. The independent committee will advise the treating physician whether or not to abandon conservative management and proceed to elective resection. The final decision is made by the treating physician.

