### Sample size

The sample size calculation is based on the minimum important difference* (MID) of the GIQLI score. The MID can be estimated by taking half a standard deviation of a quality of life instrument [7,8].

Based on the studies of Forgione et al and Zdichavsk et al the MID of the GIQLI score is estimated at 10 points [5,6]. They also demonstrated that patients improve with 10 points on the GIQLI score one month to one year after elective resection (111 ± 20.4 and 105.8 ± 15.5) for diverticulitis compared to preoperatively (100 ± 22.1 and 95.3 ± 21.4). In conclusion, a difference of 10 points corresponds with the MID and the expected improvement after elective resection.

To demonstrate this difference using an independent t-test (alpha = 0.05, delta = 10, sigma = 21, power = 0.9) approximately N = 97 patients per group are needed for this study. Therefore a total study population of 194 patients is required to attain statistical significance.

To compensate for a potential loss to follow-up of 10%, 214 patients will be included.

** Minimum important difference (MID): The smallest difference in score in the domain of interest which patients perceive as beneficial and which would mandate, in the absence of troublesome side effects and excessive cost, a change in the patient's (health care) management*.

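### A single published block size of 6 within centre-by-criterion strata lets a recruiter who tracks the stratum know up to a quarter of allocations in advance

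*Protocol article*

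**What the plan says.** The Randomisation section of the protocol article fixes one block size and the strata within which blocks run: "randomisation will be performed centrally by the study coordinator using block randomisation (block size 6) stratified for center and inclusion criteria". The same section says that "patients are informed about the study protocol by their treating physician". A three-day reflection period, a further contact and a consent visit follow, and only then is the allocation made: "After receiving this consent form, randomisation will be performed centrally by the study coordinator".

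The article does not use the word unblinded. The treatments make the allocation visible all the same: "Patients randomised for elective surgery will undergo an elective colonic resection within approximately 6 weeks", while the other arm receives whatever conservative care the treating physician prefers (Conservative treatment section).

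The allocation ratio is not stated. Equal groups are implied by the Sample size section: "approximately N = 97 patients per group are needed for this study". The same section sets the total: "To compensate for a potential loss to follow-up of 10%, 214 patients will be included". The number of centres is not given. The article mentions neither varying block sizes nor any step to keep the block size from sites.

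**The concern.** When the block size is known and past allocations are visible, the end of each block can be worked out by counting. Stratifying by centre makes the counting local: the allocations that determine the next one are those of the same hospital. The person placed to count also informs patients about the trial, and so influences whether and when a patient enters.

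The Background section supplies a possible motive. It describes reluctance among gastroenterologists and surgeons to resect after a recurrence. It also describes many physicians and patients giving up conservative care in favour of resection. Opposing preferences of this kind are the setting in which predictable allocation does most harm.

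At stake is the comparability of the arms on a patient-reported primary outcome, the GIQLI. If patients with milder or more severe complaints were steered towards the arm expected next, the treatment comparison would carry that selection with it.

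**Working it through.** The plan states no predictability figure, so there is none to reproduce.

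**Inputs.** Block size 6 and strata of centre by two inclusion criteria (Randomisation section); 214 patients, equal groups and sigma 21 (Sample size section). Assumptions: three patients per arm in each block; 3 to 40 centres; patients spread evenly at random over the strata.

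**Step 1: certain allocations in a complete block.** There are C(6,3) = 20 equally likely orderings. An allocation is certain once one arm is used up in the block.
- Positions 1 to 3: never certain.
- Position 4: certain if the first three are all the same arm, 2/20 = 0.10.
- Position 5: certain if the last two are the same arm, 8/20 = 0.40.
- Position 6: always certain, 1.00.

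The sum is 0.10 + 0.40 + 1.00 = 1.5, and 1.5/6 = 25%. The closed form for a block of 2m agrees: 2m/(m + 1) = 6/4 = 1.5.

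**Step 2: best guess.** Always guessing the arm with more places left gives m + (4^m/C(2m,m) − 1)/2 correct guesses per block. For m = 3 this is 3 + (64/20 − 1)/2 = 4.1 of 6, or 68.3%, against 50% by chance.

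**Step 3: whole trial, with incomplete last blocks.** A stratum of n patients has 1.5 × (number of complete blocks) certain allocations, plus those in the remainder: 0 for up to 3 patients, 0.10 for 4, and 0.10 + 0.40 = 0.50 for 5. For example, n = 12 gives 3.0/12 = 25%, but n = 11 gives (1.5 + 0.5)/11 = 18%. Averages over 1,000 simulated trials of 214 patients:

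| Assumed centres | Mean patients per stratum | Certain allocations |
|---|---|---|
| 3 | 214/6 = 35.7 | 23.5% |
| 5 | 214/10 = 21.4 | 22.6% |
| 10 | 214/20 = 10.7 | 20.1% |
| 20 | 214/40 = 5.4 | 14.8% |
| 30 | 214/60 = 3.6 | 8.8% |
| 40 | 214/80 = 2.7 | 5.1% |

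**Step 4: what the planned baseline adjustment would catch.** The Statistical analysis section tests large baseline differences at p < 0.05 and adjusts for the significant ones. Suppose the baseline GIQLI is among the characteristics tested, with an SD of 21 and 214/2 = 107 patients per arm. The standard error of the baseline difference is 21 × √(2/107) = 2.87. A difference of up to 1.97 × 2.87 = 5.7 points would not be significant and would not trigger adjustment under this rule. That is more than half of the 10-point minimum important difference.

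**Step 5: effect of varying the block size.** An observer was simulated who knows the set of sizes but not their order (4,000 sequences of 12 patients and 4,000 of 24).

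| Block sizes | Certain, 12 / 24 patients | Best guess right, 12 / 24 patients |
|---|---|---|
| Fixed 6 | 25.0% / 25.1% | 68.4% / 68.3% |
| 4, 6, 8 | 2.5% / 2.5% | 66.4% / 67.3% |
| 4, 6 | 6.4% / 5.8% | 67.8% / 68.7% |
| 2, 4, 6 | 3.4% / 3.8% | 69.2% / 69.7% |

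**The case against.** The case against is substantial. Randomisation is central and follows receipt of signed consent, so nobody at a site holds the list. Certain prediction needs a recruiter who knows every earlier allocation in the stratum. A centre may have several treating physicians, and nothing says that each knows the others' allocations. The Inclusion criteria section admits patients who meet both criteria, whereas the strata are described as one or the other, so a tracker may not know which stratum such a patient entered. The physician approaches the patient at least three days before allocation, without knowing whether this patient will consent or whether another will be randomised first. Slow strata, where that delay matters less, are also those most often left with incomplete blocks.

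All of this stands, and it lowers the size of the problem. None of it removes the deduction for a single active recruiter at a busy centre.

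Four stronger readings are tempting, and the documents do not support them:
- **That a quarter of the trial's allocations are predictable.** A quarter holds for complete blocks and a perfect tracker; the trial-level share is lower and depends on an unstated number of centres.
- **That selection bias has occurred.** Nothing in the article shows this.
- **That no analysis could deal with it.** Quality of life is measured at baseline, so selection on measured severity could be partly exposed and adjusted for. Selection on unmeasured features could not.
- **That varying the block size would cure the 68% best-guess rate.** Step 5 shows that this rate hardly moves.

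Only a journal article is at hand, so whether site documents disclose the block size is unknown.

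**Conclusion.** The point holds as a design weakness that is cheap to improve, not as an error in a figure or a contradiction. With one known block size, visible treatments and blocks nested within centre, a recruiter who tracks the stratum could be certain of up to 25% of allocations in complete blocks. Over the assumed range of 3 to 40 centres, the trial-level share runs from about 23.5% down to about 5%, still for a perfect tracker.

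This rests on a three-to-three split within blocks, which equal groups imply but the article does not state, and on an even spread of patients over strata. That the allocation is visible is an inference from the treatments, though a safe one. The planned adjustment triggered by significant baseline differences is not a reliable safeguard.

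**What to change.** For patients not yet randomised, replace the remaining list with a computer-generated one that keeps both stratification factors and draws block sizes at random, for example from 4, 6 and 8. Do not disclose the sizes or their order to sites. The gain does not depend on the set of sizes staying secret, because the simulated observer was allowed to know it. Avoid including a block size of 2, which leaves the best-guess rate slightly higher than under fixed blocks of 6.

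The cost is the preparation of a new list and a slightly larger possible imbalance between arms in small strata. The strata and the sample size are unchanged. The change should be described as removing near-certain allocations, because a best guess would still be right about two times in three.

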### Data collection

Data are collected by a local research fellow and/or treating physician at baseline, postoperatively (if randomised for elective resection), during outpatient visits and in case of adverse events leading to hospitalisation during follow-up. Case record forms on paper are used and faxed to the data manager.

Patients are asked to fill out HRQoL questionnaires at baseline. These questionnaires, as well as resource use and productivity losses questionnaires, are also sent to the patients at 3,6,9,12,24 and 36 months follow-up.

Data integrity will be checked when receiving the questionnaire. Any missing items will be collected by contacting the patient by telephone. Reminders (including a new copy of the questionnaire) will be send after two weeks.

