### Secondary endpoints

1. Mortality defined as:

○ *Elective surgery*: 30-days mortality.

○ *Both groups*: Mortality associated with the development of complications related to diverticulitis during follow-up.

2. Morbidity defined as:

○ Diverticulitis recurrence

○ Perforation (with purulent/fecal peritonitis)

○ Fistula

○ Symptomatic stenosis

○ Abscess

○ Stoma formation

○ Emergency surgery or re-operation

○ Peri- and postoperative complications

3. Direct health care costs. In-hospital resource use will be recorded. During follow-up medication use, general practitioner and specialist visits will be measured at baseline and regular intervals with customized questionnaires.

4. Indirect non-health care costs, using a standardised ShortForm-health and labour questionnaire (SF-H&L) at baseline and regular intervals during follow-up.

All questionnaires are asked to be filled in at baseline and 3, 6, 9, 12, 24 and 36 months after treatment

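### Post-operative data collection is tied to the assigned arm although conservative-arm patients may be operated on, and the mortality endpoint is asymmetric and not all-cause

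*Protocol article*

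**What the plan says.** **Collection.** The Data collection section lists the occasions on which the research fellow or physician records data: baseline, then "postoperatively (if randomised for elective resection), during outpatient visits and in case of adverse events leading to hospitalisation during follow-up". Only the post-operative occasion depends on the assigned arm.

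**Surgery in the conservative arm.** The Randomisation section has events in both arms managed conservatively "unless there is an absolute indication for surgery according to the treating physician". For conservative-arm patients with unbearable symptoms, an independent committee may be asked to advise "whether or not to abandon conservative management and proceed to elective resection". "The final decision is made by the treating physician".

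**Morbidity endpoint.** The secondary endpoints include "Peri- and postoperative complications" and "Emergency surgery or re-operation", neither limited to an arm. The Statistical analysis section puts all analyses on an intention-to-treat basis.

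**Mortality endpoint.** There are two items. Under the label *Elective surgery* stands "30-days mortality". Under the label *Both groups* stands "Mortality associated with the development of complications related to diverticulitis during follow-up". All-cause mortality over follow-up is not listed.

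**The concern.** The Study objective section asks whether resection is superior at a price in morbidity and mortality that is acceptable. The secondary endpoints supply that price, so both arms need the same ascertainment of it.

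The endpoint list and the collection schedule do not match. The list needs operative harms from every patient who is operated on, while the schedule has a post-operative step for one arm only. In an open trial, a dedicated step in one arm and indirect routes in the other tend to find more events in the arm with the dedicated step. For morbidity, that makes surgery look worse than it is.

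The mortality items raise a separate problem of definition, which better data capture would not cure. Some deaths after surgery belong to neither item, and which deaths count may depend on the arm. Leaving out late operative deaths can make surgery look better. Counting every death for 30 days in one arm but only attributed deaths in the other can make it look worse.

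**Working it through.** No figure in the plan bears on this point, so the check is mainly a comparison of sections.

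**1. Complications of an operation in the conservative arm**

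- *Post-operative step (Data collection):* not scheduled, because the patient was not randomised to resection.
- *Adverse event leading to hospitalisation (Data collection):* would usually be triggered by an operation for an absolute indication. A complication arising while the patient is already admitted for an elective crossover resection does not itself lead to hospitalisation, so it need not trigger this step.
- *Outpatient visits (Data collection):* open to both arms and would catch some complications later.
- *Cost records (Economic evaluation):* operations and complications are among the cost items in both arms, but they are recorded there for costing.
- *Severe adverse event reports (Patient safety):* cover both arms, but go to the ethics and safety committees. The article does not say that they feed the morbidity endpoint.

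The gap is therefore partial. It is widest for complications within an elective crossover admission.

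**2. Which deaths the mortality endpoint counts**

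| Death | 30-day item, if *Elective surgery* means the arm | 30-day item, if it means the procedure | *Both groups* item |
|---|---|---|---|
| Surgical arm, within 30 days of the elective resection | counted | counted | only if attributed to diverticulitis |
| Surgical arm, operative complication after day 30 | no | no | only if attributed to diverticulitis |
| Conservative arm, within 30 days of an elective crossover resection | no | counted | only if attributed to diverticulitis |
| Conservative arm, within 30 days of an emergency operation | no | no | plausibly, as the indication is usually a complication of diverticulitis |
| Conservative arm, operative complication after day 30 | no | no | only if attributed to diverticulitis |

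The second and fifth rows are gaps on either reading. The third is a gap in the 30-day item on the arm reading only.

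**3. Size, on assumed rates**

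Inputs: 214 patients (Sample size section), so 214 / 2 = 107 per arm. The crossover rate c and the operative complication rate r are not in the documents; 10-30% is assumed for each.

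Conservative-arm complications at stake = 107 × c × r

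- c = 0.10, r = 0.10: 107 × 0.10 × 0.10 = 1.1, or 1% of the arm
- c = 0.20, r = 0.20: 107 × 0.20 × 0.20 = 4.3, or 4% of the arm
- c = 0.30, r = 0.30: 107 × 0.30 × 0.30 = 9.6, or 9% of the arm

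Suppose that everyone in the surgical arm is operated on and r is the same in both arms. The true intention-to-treat risk difference is then r − c × r. If no crossover complication were captured, the observed difference would be r. At c = r = 0.20 that is 0.20 against 0.20 − 0.04 = 0.16, an overstatement of 4 percentage points. Over the whole range the overstatement is 1 to 9 points.

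These are ceilings. They assume that no other route captures anything, and c includes operations for an absolute indication, which would normally trigger collection through hospitalisation.

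For mortality, one death is 1 / 107 = 0.9 percentage points of an arm. If deaths are few, the classification of one could change the contrast.

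**The case against.** A reader might infer that the harms of crossover operations drop out of the comparison altogether. The documents do not support that. The morbidity list has no arm restriction, so under intention to treat a recorded complication of a crossover operation already counts in the conservative arm. Outpatient visits, hospitalisations for adverse events, cost records and severe adverse event reports all cover both arms. Under-recording is a risk created by the schedule, not an established fact.

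A reader might also infer that 30-day mortality is defined only for patients randomised to surgery. The label is *Elective surgery*, which may mean the procedure. The contrast with *Both groups* favours the arm reading but does not settle it. Deaths after operations for an absolute indication also plausibly fall under the diverticulitis-related item.

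Three further objections have weight. Thirty-day plus cause-specific mortality is a coherent choice in itself. The arm restriction stands in a one-sentence summary in a condensed article whose case record forms are not shown. The rates in the illustration are assumed, and the trial is sized on the GIQLI, not on harms. Who attributes cause of death, and whether blind to treatment, is commonly left to fuller documents and forms no part of this point.

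What these objections do not remove is that the restriction is written down rather than merely left unstated, and that it conflicts with an endpoint list open to both arms. Nor do they place a late operative death not attributed to diverticulitis in either mortality item.

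**Conclusion.** The point holds as unequal ascertainment and an asymmetric mortality definition, not as complete omission of crossover harms.

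- **Morbidity:** followed as written, the plan collects post-operative data systematically in one arm and only indirectly in the other. The effect is at most about 1 to 10 conservative-arm complications, or 1-9% of 107 patients, if crossover and complication rates are each 10-30%. The real loss is smaller to the extent that the other routes work. The likely direction is against surgery.
- **Mortality:** an operative death after day 30 not attributed to diverticulitis is outside the endpoint in either arm. A 30-day death after an elective crossover resection is also outside the 30-day item if *Elective surgery* means the assigned arm. Few such deaths are to be expected, and the direction can go either way.

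The GIQLI analysis is not affected. The correction is worth making because these endpoints carry the harm side of the trial's question and the change is cheap.

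**What to change.** 1. In the Data collection section, make the post-operative step apply after any colonic resection in either arm, whenever it occurs during follow-up. State that the resulting complications are analysed by randomised arm. This brings the section into line with the morbidity list.
2. In the secondary endpoints, define mortality as death from any cause from randomisation to 36 months in both arms. Keep 30-day mortality, after any colonic resection in either arm, and diverticulitis-related mortality as supportive items. This also removes the ambiguity in the *Elective surgery* label.

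The cost is two wording changes and the existing post-operative collection for a few more patients: about 11 to 32 if 10-30% of the conservative arm are operated on (107 × 0.10 = 10.7; 107 × 0.30 = 32.1). No treatment, visit or sample size changes.
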